### Study Aims

There is a growing interest in exploring the effect of adding mirror therapy as a biofeedback tool in fNMR, particularly in patients with peripheral facial palsy dealing with sequelae 3-12 months after onset. Therefore, the general aim of this protocol is to compare the potential effects of adjunctive mirror therapy with the gold standard fNMR on facial function and rehabilitation in nonflaccid facial paralysis. The specific objectives of this study are (1) to measure the effects of combined therapy compared to fNMR alone on participants’ facial symmetry and facial synkinesis, (2) to measure the effects of combined therapy versus fNMR alone on the quality of life and psychological aspects of the participants, and (3) to measure the effects of combined therapy versus fNMR alone on motivation and treatment adherence.

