### Recruitment and Compensation

As determined, thanks to a power calculation measure based on Martineau et al [22] to reach a power of 0.8 with a size effect of 0.6 and an α of .005, 90 patients with peripheral facial palsy of diverse etiologies in the paretic (n=30), early synkinetic (n=30), or chronic synkinetic phase (n=30) will be recruited to the study. They will then be randomized into 2 groups, mirror therapy plus fNMR or fNMR alone, by computerized block randomization. No compensation or incentive is planned to be provided at this time. Recruitment is planned to be conducted in 3 tertiary care centers (hospitals) in Canada, England, and Belgium (Hôpital Maisonneuve-Rosemont, Queen Victoria Hospital, and Sint-Augustinus GZA Hospital, respectively). A telehealth option will be available for the participants via institutionally secured platforms.

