### Measures

For data collection, each measure will be taken at baseline, 3 months, 6 months, and 1-year postintervention. Evaluation sessions will be recorded, allowing 3 independent evaluators to blindly assess the objective outcome measures. The final assessment (T3) will measure the training retention of participants following therapy sessions.

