### Statistical Analysis

As mentioned, a power calculation was done based on a previous study [23] for the primary outcome (changes from baseline to 6 months). Every measure of facial symmetry and synkinesis will be judged by 3 assessors, blinded to group assignment. Intraclass correlation coefficients will be calculated to ensure interrater reliability, and the resulting means of the assessors’ findings will be used for further statistical analysis. We will first gather descriptive statistics to provide summary data. Then, for continuous variables (Emotrics measurements, Sunnybrook global score, FNGS 2.0 global scores, FACE score, FDI, and intrinsic motivation inventory), a mixed model analysis with patients as random variables and time+group assignment as fixed variables will be considered, with auto-regressive covariance structure, given the structure of the time points for the assessments. Comparison between the timing of recruitment after PFP onset (3-6 months after onset vs 6-9 months vs 9-12 months) and outcomes at T2 and T3 will be specifically measured using multilevel analysis. Kruskal-Wallis analyses will be considered for ordinal variables (synkinesis subscores, symmetry subscores, and motivation subscores). Finally, chi-square analysis will be considered for dichotomous variables (adherence yes or no). Data will be encoded with Excel sheets, and SPSS (IBM Corp) will probably be used for statistical analysis.

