### Strengths and Limitations

The primary strength of this protocol lies in its international multicentric collaboration, which will facilitate the examination of a substantial number of participants representing diverse etiologies of peripheral facial nerve palsy (n=90, with 45 patients per group). The randomized controlled trial design used in this study allows for assessing the potential additional benefits of incorporating mirror therapy into the rehabilitation of PFP. This investigation has the potential to contribute to an evidence-based approach for clinicians involved in the care of these patients.

However, the study design does have certain limitations. First, it is not feasible to blind both the patients and treating clinicians to the assigned conditions, which could introduce bias in terms of motivation and perception of treatment efficacy. To mitigate these risks, blinded judges will be involved in assessing participants, and therapists will use a standardized feedback approach in both therapy sessions and assessments. Additionally, using Emotrics will allow for more objective facial metrics at each assessment time point [33,45]. Second, the inclusion of paretic patients in the study poses a potential confounding factor due to the occurrence of spontaneous recovery in certain cases of facial palsy [3]. However, the large number of participants and their enrollment at least 3 months after the onset of symptoms should help mitigate potential biases. It is worth noting that in Bell palsy, the most common cause of PFP, approximately 70% of patients experience full recovery within 3 months of onset [3]. The advantage of including patients across such a broad timeframe (3-12 months after onset) is to recruit a cohort that is as representative as possible of the clinical reality of facial rehabilitation in different countries.

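### The stated mixed model has only time and group as fixed effects, so the arm difference in change from baseline to 6 months is not one of its parameters

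*Protocol article*

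**What the plan says.** The Statistical Analysis section of the protocol article reports that "a power calculation was done based on a previous study [23] for the primary outcome (changes from baseline to 6 months"). A few sentences later it gives the model for the continuous variables (Emotrics, Sunnybrook, FNGS 2.0, FACE, FDI and the motivation inventory): "a mixed model analysis with patients as random variables and time+group assignment as fixed variables will be considered". For the correlation between visits within a patient, the article chooses an autoregressive form and gives the spacing of the assessments as its reason.

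Under Measures, "each measure will be taken at baseline, 3 months, 6 months, and 1-year postintervention", so four visits are available, the first of them before treatment. The first specific objective is comparative: "to measure the effects of combined therapy compared to fNMR alone on participants’ facial symmetry and facial synkinesis".

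The article mentions no group-by-time interaction, no baseline covariate and no change-score response. The multilevel analysis in the same section compares strata of time since onset at T2 and T3. It does not supply the arm difference in change.

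**The concern.** In a model with time and group as main effects, the arm difference is the same number at every visit. Randomisation makes that difference zero in expectation at T0, while the trial looks for a non-zero difference at T2. The arm difference in change from T0 to T2 is therefore fixed at zero by the model instead of being estimated. What the model does estimate is a weighted average of the arm differences over the visits.

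At stake is whether the reported coefficient answers the question for which the trial was sized. If T0 is among the response visits, the coefficient also understates the treatment effect, for all six continuous measures.

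**Working it through.** **Inputs from the article.** Four visits, 45 patients per arm, effect size 0.6, target power 0.8.

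**Assumptions, not in the article.** Within-patient correlation ρ of 0.3 to 0.7, visit SD of 1, complete data, and three courses of the true arm difference over T0, T1, T2, T3:
- constant: 0, 0.6, 0.6, 0.6
- build-up: 0, 0.3, 0.6, 0.6
- fade: 0, 0.3, 0.6, 0.3

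**Step 1: the plan's own figure.** The t-test calculation for effect 0.6, power 0.8 and two-sided alpha .05 gives 44.59, hence 45 per arm and 90 in total. The printed alpha of .005 gives 148 (normal) or 152 (t) in total. I therefore use two-sided .05 for power below. The printed alpha is a separate matter.

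**Step 2: what the group coefficient estimates (raw scores as response).** With balanced data it is w'δ, where δ holds the visit-specific arm differences and w = V⁻¹1 / (1'V⁻¹1). Adding a patient random intercept to V does not change w. The weight of T0 is:
- Compound symmetry (CS): 1/4 = 0.25 for any ρ.
- AR(1), equally spaced: 1/(4 − 2ρ) = 0.29, 0.33, 0.38 for ρ = 0.3, 0.5, 0.7.
- Continuous-time AR at months 0, 3, 6 and 12 with T0–T2 correlation 0.7: adjacent correlations are 0.837, 0.837 and 0.70. The unnormalised weights are 0.544, 0.089, 0.133 and 0.588 (sum 1.354), so the T0 weight is 0.544/1.354 = 0.40.

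**Step 3: size of the attenuation.**
- Constant: the share is 1 − w₀, that is 0.75 (CS), 0.71, 0.67, 0.62 (AR(1)) and 0.60 (continuous AR). In effect units this is 0.45 down to 0.36 instead of 0.6.
- Build-up: under CS, (0 + 0.3 + 0.6 + 0.6)/4 = 0.375, or 63%. Under AR(1) with ρ = 0.7 the share is 56%.
- Fade: under CS, (0 + 0.3 + 0.6 + 0.3)/4 = 0.30, or 50%. Under AR(1) with ρ = 0.7 the share is 37%.

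A simulation of 200 trials (random intercept, ρ = 0.5, constant effect 0.6) gave a mean additive coefficient of 0.444 (Monte Carlo SE 0.011; expected 0.45). The T2 interaction contrast averaged 0.588 (SE 0.014; expected 0.6).

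**Step 4: chance baseline imbalance.** The expected carry-over per unit of T0 imbalance is 1/(1'V⁻¹1). Under CS this is (1 + 3ρ)/4: 0.625 at ρ = 0.5 and 0.775 at ρ = 0.7. It is partial.

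**Step 5: change scores as response.** T0 drops out, and with equal weights on T1 to T3 the coefficient is 0.6 (constant), (0.3 + 0.6 + 0.6)/3 = 0.5 (build-up) or (0.3 + 0.6 + 0.3)/3 = 0.4 (fade). It equals the T2 value only in the constant case.

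**Step 6: power at 45 per arm, two-sided .05, normal reference.** The additive model uses variance (2/45)·w'Vw, the T0–T2 change contrast (2/45)·2(1 − ρ₀₂), and the baseline-adjusted T2 contrast (2/45)·(1 − ρ₀₂²), where ρ₀₂ is the T0–T2 correlation.

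| V, ρ | Course | Additive | Change T0–T2 | Baseline-adjusted T2 |
|---|---|---|---|---|
| CS 0.3 | constant | 0.872 | 0.672 | 0.847 |
| CS 0.3 | build-up | 0.733 | 0.672 | 0.847 |
| CS 0.5 | constant | 0.770 | 0.812 | 0.908 |
| CS 0.5 | build-up | 0.614 | 0.812 | 0.908 |
| CS 0.7 | build-up | 0.524 | 0.957 | 0.979 |
| CS 0.7 | fade | 0.366 | 0.957 | 0.979 |
| AR(1) 0.5 | constant | 0.765 | 0.642 | 0.836 |
| AR(1) 0.5 | build-up | 0.651 | 0.642 | 0.836 |
| AR(1) 0.5 | fade | 0.389 | 0.642 | 0.836 |
| AR(1) 0.7 | build-up | 0.501 | 0.805 | 0.904 |

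The last column also gains from baseline adjustment, so its gap to the additive column is not due to the missing interaction alone.

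**The case against.** The strongest reply is that the article condenses a fuller plan. It names fixed variables in prose, gives no equation, does not exclude an interaction, and says only that the model will be considered. Interactions, baseline handling and named contrasts often sit in an analysis plan, and the article never calls this model the primary analysis. Some of this stands: the plus sign may be loose shorthand, and a fuller plan may already have the right term. But the article prints the random part, the fixed part and the covariance structure. The fixed part as printed does not fit the outcome named in the same section, and nothing elsewhere repairs it. This is a stated rule that does not fit, not a detail left out.

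Three stronger readings are tempting, and the documents do not support them.
- **Dilution by T0 is certain.** It depends on raw scores being the response. The visit schedule suggests this, but the text does not say so.
- **Power is certain to be lower.** With ρ = 0.3 under CS and a constant effect, the additive test has power 0.87, against 0.67 for the change contrast and 0.85 for the baseline-adjusted one. Averaging several visits can more than offset the attenuation.
- **Baseline imbalance passes through in full.** The expected carry-over is partial, as step 4 shows.

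**Conclusion.** The point holds. As worded, the model has no parameter for the difference in change from baseline to 6 months, whichever response is used. That conclusion needs no assumption beyond reading the printed fixed effects as they stand.

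The size is conditional. With raw scores at T0 to T3 and correlations of 0.3 to 0.7, the coefficient is about 60-75% of a constant post-baseline effect, or about 56-63% of the 6-month effect under build-up. With change scores there is no loss for a constant effect, but the target is still an average over T1 to T3. At correlations of 0.5 to 0.7, power usually falls when the effect builds up or fades. It can be equal or higher at low correlation with a sustained effect. The documents give neither the correlation nor the course of the effect, so no single loss figure can be claimed.

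**What to change.** State a repeated-measures model with visit as a categorical factor, group, and group-by-visit. State how baseline enters: either T0 stays in the response with a mean common to both arms, or T0 is a covariate (interacting with visit) and T1 to T3 are the responses. Declare the group contrast at T2 as the primary estimate, and those at T1 and T3 as secondary. If an interaction was always intended, the change is one clarifying sentence.

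The cost is a few extra parameters (three for a full group-by-visit term over four visits) and no new data, visits or software. If the effect is truly constant after baseline, a T2 contrast is somewhat less precise than an average over visits. That is the price of estimating the outcome the trial was sized for. The Results section places inclusion from late 2024 and analysis in 2028-2029, so on that timetable the wording can be settled well before analysis.

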Irrespective of the etiology and group allocation (fNMR vs mirror therapy), our hypothesis posits that all patients with peripheral facial palsy enrolled in this study will experience improvements in facial symmetry, synkinesis, and quality of life [11,23,40]. Drawing on previous studies [23,41] and considering that mirror therapy appears most beneficial when initiated early, we anticipate mirror therapy to have greater benefits for patients in the paretic phase (3-6 months after onset), particularly in terms of restoring facial symmetry. Patients presenting with synkinesis at the time of recruitment should experience a decrease in synkinesis in the fNMR group, as indicated by several previous studies [4,5,7,13,14]. Similarly, a decrease in synkinesis is expected in the mirror therapy group, but no significant differences between the 2 groups are anticipated. Moreover, in line with previous findings [5,23], we expect both the fNMR and mirror therapy groups to demonstrate improvements in self-reported quality-of-life measures. Additionally, motivation is crucial in achieving positive therapy outcomes [42] and will be specifically assessed in this study. The hypothesis of greater motivation with mirror therapy is based on a previous study where patients reported that performing facial exercises while viewing a symmetrical face aided them as it represented their desired goal [41]. On the contrary, some patients may experience emotional responses when confronted with a face they perceive as “lost” due to facial paralysis.

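### The trial recruits mixed causes of palsy and expects improvement whatever the cause, yet no stated analysis uses aetiology: a modest, conditional loss of precision and a hypothesis phrase with no analysis behind it

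*Protocol article*

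**What the plan says.** - **Population.** Recruitment and Compensation plans to enrol "90 patients with peripheral facial palsy of diverse etiologies", with 30 in each of three phases defined by time since onset. Strengths and Limitations counts the range of causes among the trial's advantages. The shares of the causes are not given.
- **Allocation.** Patients go to "mirror therapy plus fNMR or fNMR alone, by computerized block randomization". No stratification by aetiology is stated, and none is ruled out.
- **Model.** In Statistical Analysis the primary outcome is the change from baseline to 6 months. For continuous outcomes, "a mixed model analysis with patients as random variables and time+group assignment as fixed variables will be considered". The one baseline factor with its own outcome analysis is time since onset.
- **Hypothesis.** Comparison With Prior Work expects that, "Irrespective of the etiology and group allocation", all enrolled patients will improve in symmetry, synkinesis and quality of life.
- **Recovery.** Strengths and Limitations discusses "the occurrence of spontaneous recovery in certain cases of facial palsy" as a possible confounder linked to including paretic patients. It adds that about 70% of Bell palsy patients recover fully within 3 months of onset.

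**The concern.** The article mixes causes on purpose and makes a statement that spans them, but the model it writes out has no term for cause and no other stated analysis has one. The model is stated, so this is more than an omission by a condensed article.

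Two things are at stake. First, if causes differ in how much patients change over the 6 months after entry, that variation stays in the residual, and a chance difference in case mix between the arms stays in the estimate. Second, the time effect in the model can show that patients improve on average. It cannot show that they improve whatever the cause, so a report could repeat that phrase with nothing behind it.

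**Working it through.** **Inputs from the article.** 45 per arm ("n=90, with 45 patients per group"). Sample size set "to reach a power of 0.8 with a size effect of 0.6 and an α of .005", taken here as a standardised mean difference of 0.6. Primary outcome: change to 6 months.

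**Inputs assumed, because the article gives none.** Two aetiology classes (for example Bell palsy and other), split evenly, differing by g = 0.5 to 0.8 SD (SD within class) in 6-month change.

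**Step 1: the plan's own figure.** A two-sample t-test with d = 0.6 and power 0.8 needs 44.6, so 45 per arm (90 in total), at two-sided alpha .05. Power at 45 per arm is then 0.804. At two-sided .005 it needs 75.9, so 76 per arm (152 in total), and power at 45 per arm is 0.49. The planned 90 matches .05, not the printed .005. That discrepancy is a separate matter; both levels are carried below.

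**Step 2: variance explained.** For an even split, R² = (g²/4)/(1 + g²/4).
- g = 0.5: 0.0625/1.0625 = 0.059
- g = 0.8: 0.16/1.16 = 0.138

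The range 0.05 to 0.14 covers both.

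**Step 3: power after adjustment.** Replace d by 0.6/√(1 − R²) in the noncentral t calculation, 45 per arm.

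| R² | adjusted d | power, alpha .05 | power, alpha .005 |
|---|---|---|---|
| 0 | 0.600 | 0.80 | 0.49 |
| 0.05 | 0.616 | 0.82 | 0.52 |
| 0.10 | 0.632 | 0.84 | 0.55 |
| 0.14 | 0.647 | 0.86 | 0.58 |

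The gain is about 2 to 6 points at .05 and 3 to 9 points at .005. This is a two-sample test on 6-month change, used as a stand-in for the repeated-measures model.

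**Step 4: chance imbalance if allocation ignores aetiology.** With K Bell cases among 90 and 45 per arm, the number in one arm is hypergeometric.

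| K | P(arms differ by at least 10 points) | P(at least 20 points) |
|---|---|---|
| 45 | 0.40 | 0.09 |
| 36 | 0.28 | 0.05 |
| 27 | 0.36 | 0.06 |
| 18 | 0.19 | 0.02 |

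The even split gives the highest values. The figures do not move smoothly with K because the counts are whole numbers. A 20-point imbalance with g = 0.8 shifts the estimate by 0.20 × 0.8 = 0.16 within-class SD. In total SD this is 0.16/√1.16 = 0.15, about a quarter of 0.6. It combines the top of the assumed gap with an event of at most about 9% probability, so it is an extreme case.

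**Step 5: would an interaction test help?** With two classes and a minority share p, the standard error of the aetiology-by-treatment interaction is √[(4/90)(1/p + 1/(1 − p))]. For an interaction of 0.6 SD at two-sided .05, power is 0.30 at p = 0.5 and 0.21 at p = 0.2. The interaction detectable with 80% power is 1.2 to 1.5 SD. A formal test is not worth planning.

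**The case against.** The strongest reply is that covariate adjustment is optional in a randomised trial. The comparison is unbiased without it, the unadjusted standard error already allows for chance imbalance, and nothing in the article shows that aetiology matters after entry. All of that stands, and it limits the point to efficiency and wording.

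Four stronger readings are tempting, and the article does not support them:

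- **That the authors treat aetiology as prognostic for the trial outcome.** The confounder they name is the inclusion of paretic patients, which is phase. The 70% figure for Bell palsy describes recovery within 3 months of onset, so before entry, and eligibility also requires a score of 4 or 5 on FNGS 2.0. It makes a link plausible but does not measure one among those enrolled.
- **That aetiology is left unbalanced at randomisation.** The article only names no strata. A condensed article may leave these to the full protocol.
- **That the hypothesis claims an equal mirror-therapy effect across causes.** It concerns improvement in both arms. An arm difference by cause would answer another question.
- **That the fix needs no new data.** Neither the eligibility criteria nor the measures say that aetiology is recorded.

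The model wording is also provisional. Even so, it is the only model given, and it leaves out a factor on which the article makes a statement of its own.

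**Conclusion.** The point holds in a limited form. The article mixes aetiologies by design and expects improvement regardless of cause, but its stated model has only time and group as fixed terms, and no stated analysis examines cause. Validity is not affected. The possible gain is a few power points: from 0.80 to 0.82–0.86 at two-sided .05, or from 0.49 to 0.52–0.58 at the printed .005. It depends on assumed R² of 0.05 to 0.14 and is zero if cause does not predict change after entry. Apart from precision, the across-cause part of the hypothesis has no analysis that could support it, whatever R² turns out to be. It is worth acting on because the change is cheap, not because the expected gain is large.

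**What to change.** 1. State that aetiology is recorded at entry, and fix a grouping in advance (for example Bell palsy versus other).
2. Add this grouping as a fixed effect together with its interaction with visit. A main effect alone would adjust the level of the outcome, not the change from baseline to 6 months. Make the treatment effect explicit as the group-by-visit contrast at 6 months.
3. Report within-patient improvement by aetiology descriptively, with no interaction test. Alternatively, remove the reference to aetiology from the hypothesis.

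Cost: with two classes and four visits, 1 + 3 = 4 fixed-effect parameters, one baseline item if it is not already collected, and a short descriptive table. No extra patients or visits are needed.

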**Methods:**

This study is a randomized controlled trial that compares the effect of fNMR combined with mirror therapy (experimental group: n=45) with fNMR alone (control group: n=45) in 90 patients with peripheral facial palsy presenting with sequelae 3-12 months after onset. Both groups will receive 6 months of rehabilitation training. Facial symmetry and synkinesis; participants’ quality of life; and their psychological factors, motivation, and compliance will be assessed at baseline (T0), 3 months (T1), 6 months (T2), and 12 months (T3) postintervention. Outcome measures are (1) changes in facial symmetry and synkinesis assessed with facial grading tools, (2) quality of life changes with patient questionnaires, and (3) therapy motivation with a standardized scale, as well as adherence to treatment with metadata. Changes in facial symmetry and synkinesis will be judged by 3 assessors blinded to group assignment. Mixed models and Kruskal-Wallis, chi-square, and multilevel analyses will be conducted according to the appropriate variable type.

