**Figure 2 figure2:**
[figure not shown]
Overall study design. Participants in the control group and in the experimental group are assessed at baseline (T0), 3 months postintervention (T1), 6 months postintervention (T2), and 12 months postintervention (T3). fNMR: facial neuromuscular retraining.

Frequency and length of appointment.SessionsSession 1 (1 hour to 1 hour and 30 minutes) for initial assessment and start of management.Session 2 (1 hour) 1 month after session 1.Session 3 (1 hour) 1 month after session 2.Session 4 (1 hour) generally 1-2 months after session 3.Session 5 (1 hour) is generally 3 months after session 4.Session 6 (1 hour) final session generally 6 months after session 5, then discharge to continue independently.The total treatment course will last 12 months.2-3 sessions of 10 to 15 minutes of daily home rehabilitation are expected to be done by the patients from baseline until 12 months.

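### Visits at 0, 3, 6 and 12 months do not support an auto-regressive covariance indexed by visit; specify an unstructured one

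*Protocol article*

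**What the plan says.** The Statistical Analysis section says that, for the continuous outcomes, "a mixed model analysis with patients as random variables and time+group assignment as fixed variables will be considered", and adds "with auto-regressive covariance structure, given the structure of the time points for the assessments". It gives neither the order of the auto-regression nor whether lags are counted in visits or in months. The same section names the change from baseline to 6 months as the primary outcome.

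The Measures section sets the schedule: "each measure will be taken at baseline, 3 months, 6 months, and 1-year postintervention". It gives the last visit the purpose of measuring how well training is retained. The abstract agrees on the visits: outcomes "will be assessed at baseline (T0), 3 months (T1), 6 months (T2), and 12 months (T3) postintervention".

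The length of the intervention is given in two ways, which matters if those visit times are counted from its end. The abstract says "Both groups will receive 6 months of rehabilitation training". The session textbox under Figure 2 says "The total treatment course will last 12 months".

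**The concern.** A visit-indexed auto-regressive structure gives every pair of neighbouring visits the same correlation. Here it would treat T2 and T3, 6 months apart, as being as closely related as T0 and T1, 3 months apart. Unequal spacing is a reason against that structure, yet the plan offers the spacing as the reason for it.

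Two contrasts are at stake. T0–T2 is the primary change, and a standard error that is too large there costs power. T2–T3 is the period over which retention would be judged, and a standard error that is too small there raises the false-positive rate.

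**Working it through.** **Inputs.** From the article: visits at 0, 3, 6 and 12 months, 45 patients per arm, random patient effect. Assumed, because the article gives none: correlation c at 3 months, from 0.5 to 0.9, decaying with calendar time (so c² at 6 months and c⁴ at 12), equal variances, complete data. The plan states no standard error or correlation, so there is no figure of its own to reproduce on this point.

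**Fitted model.** In large samples the fitted covariance V minimises log|V| + tr(V⁻¹S), where S is the true covariance. For a first-order visit-indexed structure with equal variances, the fitted lag-one correlation r is the mean of the three neighbouring correlations: r = (c + c + c²)/3. Numerical minimisation gives the same r. With a random patient intercept added, its variance goes to zero under this decay, so the result does not change.

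**Ratio of model to true standard error** for a between-group difference in change (the factor for 45 per arm cancels):
- T0–T2: √[(1 − r²)/(1 − c²)]
- T2–T3: √[(1 − r)/(1 − c²)]
- T0–T3: √[(1 − r³)/(1 − c⁴)]
- Actual error of a nominal 5% test: 2Φ(−1.96 × ratio)

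| c | r | T0–T2 | T2–T3 | T2–T3 error | T0–T3 |
|---|---|---|---|---|---|
| 0.5 | 0.417 | √(0.826/0.750) = 1.050 | √(0.583/0.750) = 0.882 | 8.4% | 0.995 |
| 0.7 | 0.630 | √(0.603/0.510) = 1.087 | √(0.370/0.510) = 0.852 | 9.5% | 0.993 |
| 0.8 | 0.747 | √(0.442/0.360) = 1.109 | √(0.253/0.360) = 0.839 | 10.0% | 0.994 |
| 0.9 | 0.870 | √(0.243/0.190) = 1.131 | √(0.130/0.190) = 0.827 | 10.5% | 0.997 |

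For T0–T2 the actual error falls below nominal, from 4.0% (c = 0.5) to 2.7% (c = 0.9). The group main effect in the additive time-plus-group model has a ratio of 1.00.

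**Power for T0–T2**, taking the article's effect size of 0.6 as standardised on the change. The noncentrality is 0.6 × √(45/2) = 2.846.
- Two-sided .05: Φ(2.846 − 1.960) = 81%. With ratios 1.05 and 1.13 it is Φ(2.846 − 2.058) = 78% and Φ(2.846 − 2.217) = 74%.
- Two-sided .005, the level stated under Recruitment and Compensation: Φ(2.846 − 2.807) = 52%, falling to 46% and 37%.

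The stated .005 does not reproduce 90 patients. It needs 2(2.807 + 0.842)²/0.6² = 74 per arm, while .05 needs 44 per arm. That is a separate matter, and is why both levels are shown.

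**Other correlation patterns, random patient effect fitted (all assumed):**
- Patient effect 50% of variance, remaining 3-month correlation 0.3: T0–T2 1.02, T2–T3 0.92 (error 7.1%).
- Patient effect 60%, remaining correlation 0.2: 1.01 and 0.94 (6.4%).
- Decay at 0.8–0.9 plus 20% measurement noise: 1.07–1.08 and 0.91–0.93 (6.8–7.5%).
- Constant correlation 0.6: 1.00 for every contrast.
- Patient effect 30–50% with strong remaining correlation (0.5–0.9): the ratios stay within the ranges of the table.

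**Literal post-intervention clocks.** Counting 3, 6 and 12 months from the end of a 6- or 12-month course puts the visits at 0/9/12/18 or 0/15/18/24 months, which are also unequal. With c from 0.5 to 0.9, T0–T2 is then 0.94–0.99, T0–T1 0.76–0.90 and T1–T2 1.19–1.53.

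**The case against.** The strongest reply is that the article says only auto-regressive. It does not say first-order or visit-indexed, and a continuous-time form in months would respect the spacing and fit the stated reason. The model is also only to be considered, and a condensed article may leave the exact form to an analysis plan. This stands in part: a continuous-time form is not excluded. But the bare term is normally read as visit-indexed, and the article does more than stay silent, because it makes a choice and gives a reason. If continuous time is meant, the sentence still has to say so.

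The second reply is that the size depends on a correlation pattern nobody knows. This stands. The upper figures need correlation that keeps falling with calendar time after any stable patient effect is removed.

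A reader might infer that the planned model will give wrong standard errors in both directions whatever the data. The documents do not support that: with constant correlation and the random patient effect, every contrast is right. A reader might also argue that the FNGS 2.0 entry criterion narrows baseline spread and so drives the T2–T3 error higher. A single rise in SD after baseline of 1.3 or 1.6 times gives 9.4–10.7%, close to the equal-variance result. About 13% arises only if SD keeps rising across later visits, for which the article gives no reason.

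**Conclusion.** The point holds in conditional form. On every reading of the schedule the visits are unequally spaced, so their structure does not justify a visit-indexed auto-regressive covariance.

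With visits at 0, 3, 6 and 12 months and correlation decaying in calendar time, the primary T0–T2 standard error can be 5–13% too large and the T2–T3 standard error 12–17% too small. The article states retention as the purpose of T3 but specifies no T2–T3 test, so the inflated error matters only if that contrast is tested. T0–T3 and the additive group main effect are almost unaffected.

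On this schedule a false-positive primary result should not be inferred, since the error there is conservative. On the literal post-intervention clocks the primary ratio moves slightly below 1. The direction therefore depends on a schedule that the article should reconcile with its two statements of intervention length.

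**What to change.** Replace the auto-regressive structure with an unstructured within-patient covariance over the four visits, without a separate random intercept, and with small-sample degrees of freedom. It has 4 × 5/2 = 10 parameters for 90 patients, needs no assumption about spacing, decay or equal variance, and gives a ratio of 1.00 in large samples whatever the true pattern.

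Name the fallback in advance, should the fit not converge: a continuous-time (spatial power) structure in actual months, with visit-specific variances. If the sponsor meant a continuous-time form from the start, say so in the same sentence.

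The cost is one sentence and a few more covariance parameters. The article says SPSS will probably be used, so the sponsor should confirm that the chosen software fits the fallback.
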